***5. The procedure***

**(1) The study design**: we will perform a randomized, open-label trial to assess the efficacy and safety of praziquantel, tribendimidine and mebendazole against the co-infection of helmithes. All the participants who meet the eligible criteria will be randomly assigned into four groups: Praziquantel will be administrated orally according to regional policy in Hunan: 75 mg/kg in four divided doses (twice daily spaced by 6 h for two consecutive days). Tribendimidine will be given by two means: one is a single dose of 400 mg and the other is 200 mg twice daily spaced by 6 h. Mebendazole will be given 400 mg as a single dose.

In addition, parts of participants who are assigned to be treated with tribendimidine will accept blood and urine routine checks, hepatic and renal function examinations, and electrocardiogram (ECG) examinations before and 24 h after the treatment. The abnormal indexes will be supervised and recorded.

Participants will be asked to report any potential drug-related signs and symptoms at 3 h, 24 h and 48 h after the first dose by the use of a standardized questionnaire.

Three weeks after treatment, participants were asked for two consecutive stool samples.

**(2) Preliminary survey:** To invite the residents aged 15 to 65 who lives in the Dazhongqiao and Sankoutang village , Qiyang country, Hunan province ,P.R.China to participate this trial. The name, age, sex, educational background, race and telephone will be recorded. Participants will receive containers with unique identification numbers and be invited to bring a fresh stool sample the following morning. Stool containers will then be taken to the laboratory at the Qiyang Center of Diseases Control and Prevention (Qiyang CDC). From each stool sample, three Kato-Katz thick smears will be prepared and be quantitatively examined with light microscopy for worm eggs (e.g., C. sinensis, hookworm, A. lumbricoides and T. trichiura). Number of worm eggs are counted and recorded for each parasite species separately. Patients with a microscopically confirmed co-infection with helminthes will be asked for a second stool sample.

**(3) Sample size.** Sample size was based on a suggested sample size of 12 patients per group for proof-of-concept trials. Taking into account of the patients dropping out, we will plan to enroll 40 participants per group.

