**(4) Eligibility criteria**:Eligible for inclusion is all residents of Dazhongqiao village and Sankoutang village aged 15 to 65 years old whose first stool sample to perform the Kato-Katz thick smears in preliminary survey, co-infection with helminthes, and submit the second stool sample and the written informed consent before the treatment.

**(5) Exclusion criteria**: Participants will be excluded from treatment if fulfilling any of the following exclusion criteria: pregnant (for females), the presence of any abnormal medical disorder (i.e., fever and hepatomegaly), history of any acute or sever chronic disease, psychiatric and neurological disorders, and anthelmintic treatment within the previous 4 weeks.

**(6) Informed consent**: Each of the participants will receive a written informed consent. We explain the risk and benefits on the consent form, and tell them all participants are voluntary, and individuals can withdraw from the trial at any time. If the participant is a child, the informed consent should be signed by his/her legal guardian. Written informed consent need to be obtained from each participant or legal guardians of each child before they are allowed to participate this trial.

**(7) The check-up before treatment**: all participants will be required to undergo a inquisitorial medical check-up, and the female participants aged 16 to 50 will accept the pregnancy test. Participant assigned to the two tribendimidine treatment groups will accept blood and urine routine checks, hepatic and renal function examinations, and electrocardiogram (ECG) examinations before the treatment.

Blood samples should be taken immediately to the local hospital with ice packs. Urine samples and part of blood samples should be tested within 30 min as urine and blood routine checks. The other blood samples should be stored at 4 ◦C in the refrigerator for 4 h, and then be centrifugalized. The supernatants will be tested for hepatic and renal function detection.

**(8) Take the medication**: The investigator should give the medication to participants, and ensure they will swallow it with warm water. The participant cannot take any other drugs during the experiment. If the drug is spit out within one hour after taking the medication, he/she will need to take the medication again. Both the strenuous exercise and the drinking will be forbidden during the experiment.

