**(9) Follow up:** The trial clinicians will be present, monitor acute adverse events, and provide medical assistance if necessary. Participants will be asked to report any potential drug-related signs and symptoms at 3 h, 24 h and 48 h after the first dose by the use of a standardized questionnaire. Intensity of AEs are recorded and graded as mild, moderate, severe and serious as judged by study physicians.

Mild: asymptomatic or mild symptoms; clinical or diagnostic observations only; intervention not indicated

Moderate: minimal, local or noninvasive intervention indicated.

Severe: severe or medically significant but not immediately life-threatening; hospitalization or prolongation of hospitalization indicated.

Serious: life-threatening consequences; urgent intervention indicated.

**(10) Re-examination of the stool sample**: Three weeks after treatment, participants were asked for two consecutive stool samples. Stool containers will then be taken to the laboratory at the Qiyang Center of Diseases Control and Prevention (Qiyang CDC). From each stool sample, three Kato-Katz thick smears will be prepared and be quantitatively examined with light microscopy for worm eggs (e.g., C. sinensis, hookworm, A. lumbricoides and T. trichiura). Number of worm eggs will be counted and recorded for each parasite species separately.

**(11) Primary and secondary outcomes:** Primary outcomes are the cure rate (CR) and egg reduction rate (ERR) at 3 weeks after treatment as efficacy outcomes. The CR is defined as the percentage of participants excreting eggs before treatment who became negative after treatment. The ERR is calculated as the reduction in the group’s geometric mean egg count after treatment divided by the geometric mean of the same patients before treatment, multiplied by 100. Secondary outcomes are the frequencies of adverse events (AEs) and the abnormal biochemical tests after treatment including urine and blood test, hepatic and renal function examinations and ECG.

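### The laboratory and ECG outcome in section 5(11) counts results that are abnormal after treatment without reference to the participant's own pre-treatment result, so it mixes background prevalence with change after dosing

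*Protocol*

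**What the plan says.** - **Outcome definition (Protocol 5(11)).** Besides adverse events, the secondary outcomes are the frequencies of "the abnormal biochemical tests after treatment including urine and blood test, hepatic and renal function examinations and ECG". The definition does not mention the pre-treatment result.
- **Schedule (5(1)).** The blood, urine, liver, kidney and ECG tests are done twice: "electrocardiogram (ECG) examinations before and 24 h after the treatment". On handling, the section adds only: "The abnormal indexes will be supervised and recorded".
- **Who is tested.** Section 5(1) says "parts of participants who are assigned to be treated with tribendimidine will accept blood and urine routine checks". Section 5(7), on the check-up before treatment, says "Participant assigned to the two tribendimidine treatment groups will accept blood and urine routine checks". Neither section gives these tests to the praziquantel or mebendazole groups.
- **Exclusions (5(5)).** The nearest criteria are clinical: "the presence of any abnormal medical disorder (i.e., fever and hepatomegaly), history of any acute or sever chronic disease". No laboratory value or ECG finding is named as a reason for exclusion.
- **Group size (5(3)).** "we will plan to enroll 40 participants per group", so at most 80 participants over the two tribendimidine groups.

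**The concern.** Taken literally, the outcome classifies a participant by the 24 h result alone. Someone with a raised liver enzyme before dosing and the same value a day later is counted, exactly like someone whose value was normal and became abnormal. Someone whose abnormal value worsens is counted no differently from someone whose value stays the same.

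Two features of the design make this matter. Because the other two drugs' groups are not tested, there is no background rate to set against the tribendimidine count, and the participant's own pre-treatment value is the only reference available. And because no laboratory or ECG threshold excludes anyone, some tested participants may well be abnormal before dosing.

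The same section already handles efficacy differently. The cure rate is restricted to people who were egg-positive beforehand, and the egg reduction rate is taken against the same patients' earlier counts. The laboratory and ECG outcome is the one measured outcome there that ignores a baseline the trial collects. It is also the protocol's only planned laboratory and ECG evidence on tribendimidine.

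**Working it through.** The protocol states no abnormality rate, error level or power for this outcome, so there is no figure to reproduce. The check is a comparison of two counting rules, for any one test.

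**Inputs**
- n = number tested. Upper limit 2 x 40 = 80, from 5(3) and 5(7). Since 5(1) speaks of only part of these participants, n = 40 is also shown.
- b = proportion abnormal before dosing. Not in the protocol; assumed 5%, 10%, 20%, 30%.
- s = proportion of those still abnormal at 24 h. Not in the protocol; assumed 1.0 or 0.8.
- t = proportion of the initially normal who are abnormal at 24 h. Not in the protocol; assumed 0 or 5%.

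**Formulas**
- Counted under 5(11) as worded: n x (b x s + (1 - b) x t)
- New since baseline: n x (1 - b) x t
- Difference, i.e. carried over from before dosing: n x b x s

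**Results for n = 80**

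| b | Counted, t = 0, s = 1 | Counted, t = 0, s = 0.8 | New, t = 0 | Counted, t = 5%, s = 1 | New, t = 5% |
|---|---|---|---|---|---|
| 5% | 4 | 3.2 | 0 | 7.8 | 3.8 |
| 10% | 8 | 6.4 | 0 | 11.6 | 3.6 |
| 20% | 16 | 12.8 | 0 | 19.2 | 3.2 |
| 30% | 24 | 19.2 | 0 | 26.8 | 2.8 |

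Example for the last row with t = 5%: 80 x (0.30 x 1 + 0.70 x 0.05) = 80 x 0.335 = 26.8 counted, of which 80 x 0.70 x 0.05 = 2.8 are new. With n = 40 every entry halves; the first column becomes 2, 4, 8 and 12.

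With no drug effect and full persistence, everything counted was there before dosing. With a 5% rate of new abnormality, the count rises with the baseline rate while the number of new abnormalities falls, so the count follows the background.

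**When the rule makes little difference.** If abnormality on a test came and went independently between the two occasions at 5%, then b = s = t = 0.05. The wording would count 80 x (0.05 x 0.05 + 0.95 x 0.05) = 4.0, and a normal-to-abnormal rule 80 x 0.95 x 0.05 = 3.8. Almost nothing is removed. The expected number moving from abnormal to normal would also be 80 x 0.05 x 0.95 = 3.8, which is why both directions of the shift should be shown.

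**The case against.** **The clause is a label, not a counting rule.** Testing the same people before and after dosing only makes sense if the two are to be compared, and the sentence about recording abnormal indexes is not limited to the 24 h tests. This is fair as to likely intent, and it limits the weight of the point. It does not change the wording: 5(11) specifies the post-treatment result and nothing else.

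**The analysis plan would settle this.** Shift tables and paired changes are ordinary content for a statistical analysis plan, and one may exist. For that reason the silence of 5(12) on these tests is not held against the protocol. What remains is the outcome definition itself, which the protocol does state.

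**Stronger readings that the text does not support**
- A reader might infer that the protocol will attribute pre-existing abnormalities to tribendimidine. No section says so; it says only that they fall within the count.
- A reader might infer that helminth infection makes the background rate high. The protocol gives no rate of laboratory or ECG abnormality and no statement to that effect.
- A reader might size the problem by the chance that a healthy person has at least one value outside its reference range among many tests. That describes a single occasion, whereas the defect lies in abnormalities carried over from before dosing, so persistence governs the size. The outcome is also expressed per test, not as any abnormality among several.
- A reader might infer that abnormal pre-treatment results have no consequence for anyone's treatment. The tests belong to a pre-treatment check-up and the clinical exclusions are broad. The text supports only the narrower statement that no laboratory or ECG threshold is given.

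**Conclusion.** The point holds as a defect in a stated outcome definition. As worded, the laboratory and ECG outcome combines what was already present before dosing with what changed afterwards, and no comparator arm or exclusion threshold separates the two.

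Its size is unknown. On the assumptions of 80 tested, full persistence and no drug effect, baseline rates of 5% to 30% give 4 to 24 counted participants per test with none new; at 80% persistence the range is 3.2 to 19.2. If abnormalities did not persist at all beyond chance, the effect would be close to nil.

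This concerns a secondary safety outcome, and the pre-treatment data are already to be collected, so nothing is lost if the wording is corrected before analysis. The change is worth making because it is nearly free, not because the documents show that a wrong safety conclusion will follow.

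**What to change.** 1. In 5(11), define the outcome as tests that were normal before treatment and abnormal at 24 h, with participants normal on that test before treatment as the denominator.
2. Report a before/after shift table for each test, including abnormal-to-normal moves, so that the reader can judge how much of the normal-to-abnormal traffic could be chance.
3. For continuous indices, report the paired change from the pre-treatment value. This shows worsening in values already abnormal or still within range, which the new count would miss.
4. Reconcile 5(1), where part of the tribendimidine participants are tested, with 5(7), where the pre-treatment tests apply to both tribendimidine groups. The paired outcome needs one stated tested set.

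**Cost.** A change of wording and one extra table; no additional tests or participants.

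**What it does not solve.** Chance crossings remain, because no other arm is tested. For tests read only as normal or abnormal, worsening of an existing abnormality will still not show; counting it would need a laboratory and ECG grading scale, which the protocol does not contain.

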**(12) Statistical analysis.** All data will be double entered, and the per-protocol analysis will be pursued. Statistical analyses will be done with SAS software (version 9.1). The numbers of every kind of worm eggs recorded from 6 Kato-Katz slides before and after treatment will be added to calculate the arithmetic mean of eggs per gram of stool (EPG) for every participant. The arithmetic means is used to determine the infection intensity, and the geometric EPG is calculated to assess the egg reduction rate among the treatment groups. Logistic regression models will be used to examine cure rates of helminthes in different treatment groups. Negative binomial regression analysis will be adopted to compare egg reduction rates of helminthes between four groups. Pearson’s χ2 test will be applied to compare the proportion of reported adverse events between the treatment groups. Negative binomial regression models will be used to compare the number of adverse events in the treatment groups.

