***9. Preparation for the AEs***

In order to deal with the possible cases of severe adverse reaction caused by the treatment, cooperative hospital should prepare an ambulance. When it is necessary, the ambulance will immediately rush to the scene. Some drugs will be prepared, such as epinephrine injection, antihistamine, antiemetic, antipyretic analgesic, antispasmodic drugs and other conventional aid medicines.

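### The per-protocol statement in section 5(12) is not limited to efficacy and no all-treated safety set is named, so treated participants could leave the adverse-event comparisons along with their recorded data

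*Protocol*

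**What the plan says.** Section 5(12) of the protocol names one analysis population: "All data will be double entered, and the per-protocol analysis will be pursued". It then sets out the efficacy models and, in the same paragraph, two safety comparisons: "Pearson’s χ2 test will be applied to compare the proportion of reported adverse events between the treatment groups" and "Negative binomial regression models will be used to compare the number of adverse events in the treatment groups". Neither safety sentence gives its own population. No section of the protocol names an all-treated or safety set, and none defines per-protocol.

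Section 1 makes safety part of the objective. Section 5(11) lists AE frequencies and abnormal laboratory and ECG results as secondary outcomes, and labels the cure rate and egg reduction rate as the efficacy outcomes. Under section 5(9), a symptom questionnaire is given 3, 24 and 48 hours after dosing starts. The efficacy material comes much later: "Three weeks after treatment, participants were asked for two consecutive stool samples" (section 5(10)).

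**The concern.** A per-protocol set commonly leaves out people who did not complete treatment or who lack the outcome measurement. For efficacy that is a choice the sponsor may make. For safety it is unsuitable, because a person who took the drug and had an AE is informative whether or not the remaining doses were taken or a stool sample was returned three weeks later.

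The one population that the protocol fixes therefore does not suit half of its objective. If it is applied to the AE tests, some AE data already collected would not be used. Where the AE itself is the reason for leaving, for example when a participant declines the next dose, the AE rate of that arm would be understated.

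**Working it through.** The protocol states no figure on this point that could be reproduced: it gives no AE rate, stopping rate or exclusion rate. The check is therefore a reading of the sections together, followed by an illustration on assumed counts.

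**Step 1: does the wording limit per-protocol to efficacy?** No. The clause carries no qualifier, and the AE analyses follow in the same paragraph. The opening words about all data belong to data entry, so they do not settle the matter either way.

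**Step 2: can AEs be on record before a participant leaves the set?** Yes.
- Missing stool samples: the last AE questionnaire is at 48 hours and the samples are due at three weeks. This applies in all four arms.
- Incomplete dosing: section 5(1) gives praziquantel as four doses over two days and split-dose tribendimidine as two doses 6 hours apart. Three of the four praziquantel doses and one of the two split tribendimidine doses fall after the 3-hour questionnaire. In the single-dose tribendimidine and mebendazole arms, none does.
- Withdrawal is allowed at any time (section 5(6)), and the 40 per group in section 5(3) already allows for dropout, at no stated rate.

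**Step 3: what could exclusion do to a reported rate?** The input from the protocol is n = 40 per arm. Assumed inputs are *a* participants with an AE, of whom *d* are excluded, and *u* excluded participants without an AE.

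Reported rate = (a − d) / (40 − d − u)

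With a = 20, so that the all-treated rate is 20/40 = 50.0%:

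| Excluded | Reported rate | Change |
|---|---|---|
| nobody | 20/40 = 50.0% | 0 |
| 4 with an AE | 16/36 = 44.4% | −5.6 points |
| 4 with and 4 without | 16/32 = 50.0% | 0 |
| 4 without an AE | 20/36 = 55.6% | +5.6 points |

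The rate is unchanged when the share of AE cases among those excluded equals the share in the arm, that is d/(d + u) = a/40. It falls when AE cases are over-represented among those excluded and rises when they are under-represented.

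For a single excluded AE case the fall is (40 − a) / (40 × 39). This is 20/1560 = 1.3 points at a = 20 and 36/1560 = 2.3 points at a = 4.

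**Step 4: between arms.** Assume 20/40 in a multi-dose arm against 10/40 in a single-dose arm, a difference of 25.0 points.
- Four AE cases lost from the multi-dose arm only: 16/36 − 10/40 = 19.4 points.
- Two AE cases lost from each arm: 18/38 − 8/38 = 26.3 points.
- Two AE cases lost from the single-dose arm only: 20/40 − 8/38 = 28.9 points.

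The difference can shrink or grow, depending on who leaves which arm.

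**The case against.** The strongest reply is that the protocol never says AEs are analysed per protocol. The AE sentences refer only to the treatment groups. Section 5(11) separates efficacy outcomes from AEs, and only the cure rate and egg reduction rate need a three-week sample. An efficacy-only reading is therefore natural, and an unseen SAP may define a safety set. This stands in part: the wording is ambiguous, and the absence of a safety set would not by itself be a finding. What remains is that the protocol does fix a population, without qualification, in the paragraph that specifies the AE tests.

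The second reply is that the ways out are hypothetical. Dosing is supervised, and a dose spat out within an hour is repeated. The background reports mild, transient AEs with tribendimidine, and nothing links failure to return a stool sample to AEs. All of this stands as a limit on size. The background does say that the WHO praziquantel schedule can be hard to complete, partly because of AEs. That schedule totals 25 × 3 × 2 = 150 mg/kg against 75 mg/kg here, so it supports no rate for this trial.

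A reader might also infer that treating an AE would remove a participant, since section 5(8) says "The participant cannot take any other drugs during the experiment" while section 9 says "Some drugs will be prepared, such as epinephrine injection, antihistamine, antiemetic, antipyretic analgesic, antispasmodic drugs". The protocol does not support this. Its clinicians may give medical help, the section 9 drugs are held for severe reactions, and nothing calls such treatment a deviation. The point does not rest on it.

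Finally, the assumed shifts are small beside sampling error. For 20/40 against 10/40 the standard error of the difference is √(0.5 × 0.5/40 + 0.25 × 0.75/40), about 10.5 points.

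**Conclusion.** The point holds as a defect of wording with a possible effect on the safety comparisons. Following section 5(12) as written could take treated participants, and AEs recorded within 48 hours, out of the AE analyses. This rests on two assumptions: that per-protocol is applied to the AE tests, and that it excludes people with incomplete dosing or no three-week sample. The protocol confirms neither.

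Neither the size nor the direction can be derived, even within one arm. In the illustration, four exclusions move a 50.0% rate to anywhere from 44.4% to 55.6%, depending on whether they had AEs, and no exclusions means no bias. Only exclusions caused by AEs have a predictable effect, which is to understate the rate.

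A reader might infer that the praziquantel and split-dose tribendimidine arms will look safer than they are, because only they have doses left to decline. That is possible, but missing stool samples can act in every arm and can remove people with or without AEs, so the documents do not support a net direction. The change is still worth making, because safety is part of the objective and the remedy is nearly free.

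**What to change.** In section 5(12), limit the per-protocol statement to the cure rate and the egg reduction rate, and add wording such as: *Adverse events will be analysed in all participants who received at least one dose of study drug, by the regimen started, whether or not dosing was completed or a three-week stool sample was given.* Run both the chi-square test and the negative binomial model for AEs on this set. Apply the same rule to laboratory and ECG results, among the tribendimidine participants who were tested.

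The cost is a few sentences and no new data collection, since the questionnaires are already planned. Reported AE rates may come out slightly higher or slightly lower than under the per-protocol set. Reporting by arm how many stopped dosing because of an AE would be useful but is optional: the protocol does not provide for recording the reason for stopping, so this would need an extra item on the form.

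### The stool sample that qualifies a participant also supplies half of the baseline egg count, so each arm's absolute egg reduction rate is inflated in light infections; randomised comparisons between arms are not biased

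*Protocol*

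**What the plan says.** - **Selection.** Protocol section 5(2) screens residents with one stool sample, then: "Patients with a microscopically confirmed co-infection with helminthes will be asked for a second stool sample". Section 5(4) makes eligible those "whose first stool sample to perform the Kato-Katz thick smears in preliminary survey, co-infection with helminthes, and submit the second stool sample". The second sample has to be handed in; it does not have to be positive.
- **Slides.** Section 5(2): "From each stool sample, three Kato-Katz thick smears will be prepared". Section 5(10) repeats this at follow-up.
- **Baseline and follow-up counts.** Section 5(12): "The numbers of every kind of worm eggs recorded from 6 Kato-Katz slides before and after treatment will be added", to give each participant's EPG.
- **Follow-up.** Section 5(10): "Three weeks after treatment, participants were asked for two consecutive stool samples". No condition is placed on their result.
- **Primary outcomes.** Section 5(11): "The CR is defined as the percentage of participants excreting eggs before treatment who became negative after treatment". The ERR rests on the "geometric mean egg count after treatment divided by the geometric mean of the same patients before treatment". Both are before-to-after figures within a group.
- **Arms.** Section 5(1) randomises to four groups: praziquantel, two tribendimidine regimens and mebendazole. All receive an active drug.

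**The concern.** For a species that qualified the participant, the first sample cannot be zero, whereas either follow-up sample can be. The baseline is pushed up by selection and the follow-up is not, so the mean count falls even if the drug does nothing. With no untreated arm, the trial cannot show how much of the fall this accounts for.

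The stated objective is to appraise efficacy, and the ERR is a primary outcome reported for each arm in absolute terms. The risk is greatest where activity is in doubt. For mebendazole against *C. sinensis*, the only specific support in the background section is from rats. A modest ERR there could be read as activity when part of it, or all of it, is selection.

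**Working it through.** **1. The plan's own figure.** Pre-treatment samples × smears per sample = 2 × 3 = 6, which matches the six slides in section 5(12). No other pre-treatment stool sample is described, so six is reached only by counting the three screening slides. The selecting sample is 3/6 = 50% of the baseline.

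**2. A hand check for one participant.** Assumptions: 24 EPG per egg per slide, a true intensity of 24 EPG (mean 1 egg per slide, 3 per sample), and gamma day-to-day variation with shape k = 1.
- P(sample is zero) = (k/(k+3))^k = 1/4 = 0.25.
- Mean of sample 1, given that it is positive: 3/(1 − 0.25) = 4 eggs.
- Baseline: (4 + 3)/6 × 24 = 28 EPG. Follow-up with no drug effect: (3 + 3)/6 × 24 = 24 EPG.
- Spurious fall in the expected count: (28 − 24)/28 = 14%.
- Sample 2 against one follow-up sample: 3 eggs against 3 eggs, so no spurious fall.
- Apparent cure on six slides: 0.25 × 0.25 = 6%. For a person of given intensity this is simply the chance that the smears miss the infection twice; selection on sample 1 does not change it.

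**3. Simulation over a population, inert drug.** 400,000 persons per scenario, four samples of three slides, selection on sample 1 > 0, one species at a time. Assumed: log-normal intensity with log-SD 1.5, gamma shape 1 to 2, geometric mean as exp(mean log(EPG + 1)) − 1. None of these values is in the protocol.

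| Median EPG | Spurious ERR, six slides | Apparent cure, six slides |
|---|---|---|
| 24 | 19–26% | 6–9% |
| 48 | 12–19% | 3–5% |
| 96 | 7–13% | 2–3% |
| 240 | 3–7% | 0.5–1% |
| 1000 | 0.6–2% | 0.2% or less |

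A second set of assumptions (log-SD 1.3, shape 3 to 0.5) gives the same pattern over a wider range: ERR 17–43% at 24 EPG, 5–28% at 100 EPG and 0.2–11% at 1000 EPG.

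**4. With real efficacy** (log-SD 1.3, shape 1). A true 50% reduction reads 61% at a median of 50 EPG and 53% at 300 EPG. A true 80% reduction reads 85% and 82%.

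**5. Where the apparent cure comes from** (log-SD 1.3, inert drug). Restricting to persons positive in both baseline samples lowers it only from 15.3% to 11.8% (24 EPG, shape 0.5), or from 4.9% to 3.5% (50 EPG, shape 1). Most of it remains.

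**6. Between arms.** Two arms of 40, inert drug, 50 EPG, shape 1: mean difference in cure 0.000; type I error 5.0% for log change and 4.2% for cure.

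**7. The companion ERR** (sample 2 against the first follow-up sample, three slides each).
- Among sample-1 positives, the spurious ERR is about 0% in every scenario.
- If participants positive only in sample 2 are added, selection now acts on sample 2 and the spurious ERR returns: 14–19% at 24 EPG, 8–12% at 48 and 4–7% at 96.

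**The case against.** The strongest reply is that the planned efficacy models in section 5(12) compare groups: logistic regression for cure and negative binomial regression for egg reduction. Allocation is randomised, so selection acts equally on all arms. This stands. A reader might infer that the comparison of the four regimens is biased; step 6 shows that it is not. The point concerns the absolute ERR of each arm, which section 5(11) names as a primary outcome.

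Second, the size is uncertain. The protocol gives neither infection intensity nor day-to-day variation, and the bias is near nil in heavy infections and small for a highly effective drug. This also stands and limits the weight of the point. It does not remove it, because the protocol sets no minimum intensity and light infections can enter.

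Third, apparent cure is largely a matter of smear sensitivity. A reader might infer that regression to the mean produces the spurious cures; steps 2 and 5 do not support that. Much of the effect would be there without selection on sample 1.

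Fourth, a companion analysis could be left to a statistical analysis plan, which is not shown. That is a fair remark about where to put the remedy. The six-slide baseline itself, however, is fixed in the protocol, so the point is not about an omission.

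**Conclusion.** The point holds for the absolute geometric-mean ERR of each arm. An inert drug would show roughly 19–26% at a median of 24 EPG, falling to 2% or less at 1000 EPG, under assumed intensity and day-to-day variation. That the screening slides are among the six is inferred from 2 × 3 = 6, but the protocol offers no other way to reach six.

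Some cure (about 6–9% at 24 EPG, about 1% or less at 240 EPG) also appears without drug effect, much of it through missed infections. Reading the reported reductions as mostly artefact would go too far: the inflation is one part of the figure, and it shrinks as true efficacy rises. The change is a cheap improvement to how a primary outcome is reported, not a flaw in the randomised comparison.

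**What to change.** In Protocol section 5(12), keep the six-slide CR and ERR and add a stated companion ERR for each species and arm:
- restrict it to participants positive for that species in the first pre-treatment sample;
- compare the second pre-treatment sample (three slides) with the first follow-up sample (three slides);
- keep the zeros.

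The restriction must be written out, because without it the bias returns (step 7).

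If a no-drug benchmark for cure is wanted, take the share of sample-1 positives who are negative in sample 2, and set it against the share of the same participants who are negative in the first follow-up sample, three slides each. It must not be set beside the six-slide CR. With an inert drug at 24 EPG the three-slide share is 17–23% and the six-slide CR is 6–9%, so a weakly active drug would look inert.

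Cost: a few sentences and a little more analysis, with no new samples or participants. The companion ERR is less precise, since it uses three slides per side instead of six, and the absolute efficacy figures may come out slightly less favourable.
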